**Behaviours:**			
- **Undertake strengthening exercise program**			
- **Undertake negotiated physical activity plan**			
**Behaviour change technique**	**Written information**	**Physiotherapist discussion**	**Other**
**Consequences of behaviour**			
Explanation of benefits of exercise & physical activity.	✓ OA Info booklet	✓ Consult #1	
Explanation that exercise & physical activity will not make joint structural damage worse.	✓ OA Info booklet	✓ Consult #1	
**Goal setting & action planning**			
Use of a plan stating how often to exercise & which exercises to do (including dosage).	✓ Knee plan & log book	✓ Consults #1–5	
Development of specific goals related to patient’s knee problems.		✓ Consult #1 & 5	✓ Pre-consultation survey
Development of specific physical activity & step goals.	✓ Knee plan & log book	✓ Consults #2–5	
**Barrier identification/planning**			
Information & discussion about barriers to exercise & physical activity adherence, including problem-solving.	✓ OA Info booklet	✓ Consults #1–5	
	✓ Knee plan & log book		
	✓ Exercise booklet		
**Behavioural grading & instruction**			
Strengthening exercises are graded in number, intensity and/or difficulty to get progressively harder over time.	✓ Knee plan & log book	✓ Consults #1–5	✓ Four graded resistance bands
	✓ Exercise booklet		
Physical activity is graded in duration, intensity and/or frequency to get progressively harder over time.	✓ OA Info booklet	✓ Consults #1–5	
	✓ Knee plan & log book		
Instruction in where, when and how to perform physical activity	✓ Knee plan & log book	✓ Consults #2–5	
Instruction in where, when and how to perform strengthening exercises	✓ Knee plan & log book	✓ Consults #1–5	✓ Four graded resistance bands
	✓ Exercise booklet		
Demonstration of how to perform strengthening exercises		✓ Consults #1–5	✓ Online video library
Encouragement to join group exercise classes.	✓ OA Info booklet	✓ Consults #2–5	
Encouraged to involve partner or family to join in with exercising & physical activity.	✓ OA Info booklet	✓ Consults #2–5	
**Self-monitoring & feedback**			
Encouraged to self-monitor exercise & physical activity	✓ Knee plan & log book	✓ Consults #1–5	✓ Activity monitor
Physiotherapist review of & and feedback on exercise & physical activity recorded	✓ Knee plan & log book	✓ Consults #2–5	✓ Activity monitor
**Relapse prevention**			
Instruction on how to modify exercise & physical activity during flare-ups	✓ Exercise booklet	✓ Consults #1–5	
Planning for set-backs in physical activity & how to overcome them		✓ Consult #2	
Dealing with lapses & set-backs with exercise & physical activity; use of constructive self-talk	✓ Exercise booklet	✓ Consult #5	
**Pain & emotional control**			
Encouragement to use activity pacing & pain coping activities (eg relaxation, pleasant imagery, mindfulness)	✓ OA Info booklet	✓ Consults #2 & 3	
Tips for healthy sleep	✓ OA Info booklet	✓ Consult #3	
**Prompts**			
Encouraged to use reminders to exercise.	✓ OA Info booklet		
**Rewards**			
Patient encouraged to use self-rewards for achieving exercise & physical activity goals	✓ OA Info booklet	✓ Consults #2–5	
Physiotherapist congratulates adherence to exercise & physical activity		✓ Consults #2–5	
**Social comparison**			
Encourage reading of patient success stories	✓ OA Info booklet	✓ Consult #5	
**Review**			
Review of behavioural goals (exercise & physical activity) at follow-up.		✓ Consults #2–5	
Review of outcomes (pain and function) at follow-up.		✓ Consults #2–5	
Review, supervision and correction of strengthening exercise technique.		✓ Consults #1–5

**Table 3 Tab3:** Strengthening exercise protocol, with progressions (where applicable)

**Maximum of 6 exercises at any one time, performed three times/week**			
2 quadriceps strengthening exercises			
1 hip abduction/gluteal strengthening exercise			
1 hamstring/gluteal strengthening exercise			
1 calf strengthening exercise			
1 other exercise as appropriate			
**1. Quads strengthening**			
**Knee extension**	Non weight-bearing	Q1. Seated knee extension	**Progression:** Increase resistance with elastic band – red through to black
	Non weight-bearing	Q2. Inner range quads over roll	
**Sit-to-stand**	Weight-bearing	Q3. Sit to stand without using hands	**Progression:** lower chair height, hover above the seat without touching down, add resistance band around knees and push outwards while performing sit to stand
	Weight-bearing	Q4. Asymmetrical chair stands (with more weight on arthritis leg)	
**Steps**	Weight-bearing	Q5. Step-ups	**Progression:** Increase step height
	Weight-bearing	Q6. Forward touch-downs from a step	**Progression:** Increase step height, don’t touch floor
	Weight-bearing	Q7. Step-ups with weight	**Progression:** Increase step height, increase weight
	Weight-bearing	Q8. Forward touch-downs with weight	**Progression:** Increase step height, increase weight
**Wall squats**	Weight-bearing	Q9. Partial wall squats	**Progression:** Halfway hold in bent-knee position, increase the amount of body weight taken through the arthritis knee.
	Weight-bearing	Q10. Split leg wall squats	
**Controlled squats**	Weight-bearing	Q11. Controlled squats (with back of chair support)	
**Controlled knee flexion/extension**	Weight-bearing	Q12. Controlled knee flexion/extension with forwards/backwards sliding of opposite leg	
	Weight-bearing	Q13. Controlled knee flexion/extension with forwards/backwards sliding of opposite leg with elastic band	**Progression:** Increase resistance by changing elastic band colour – red through to black
	Weight-bearing	Q16. Controlled knee flexion/extension with sideways sliding of opposite leg	
	Weight-bearing	Q17. Controlled knee flexion/extension with elastic band and sideways sliding of opposite leg	**Progression:** Increase resistance by changing elastic band colour – red through to black
**Step to single leg balance**	Weight-bearing	Q14. Step to standing balance on semi-flexed knee	
	Weight-bearing	Q15. Step to standing balance on semi-flexed knee with arm movements	
**2. Hip abductor/gluteal strengthening**			
**Standing hip abduction**	Non weight-bearing	HA1. Side leg raises in standing with elastic band.	**Progression**: Increase resistance by changing elastic band colour – red through to black, add halfway hold
	Weight- bearing	HA3. Wall push with opposite leg, standing on straight arthritis leg	**Progression:** Hold weight in hand, increase the hold time
	Weight- bearing	HA4. Wall push with opposite leg, standing on arthritis leg with deeper knee bending	
**Side stepping**	Weight-bearing	HA2. Crab walking with elastic band	**Progression:** Increase resistance by changing elastic band colour – red through to black
**3. Hamstring/gluteal strengthening**			
**Supine bridging**	Weight-bearing	HG1. Bridge with hold	
	Weight-bearing	HG2. Split leg bridge with hold	
	Weight-bearing	HG3. Single-leg bridge with hold	
**Standing knee flexion**	Non weight-bearing	HG4. Hamstring curls standing over bench	
	Non weight-bearing	HG5. Hamstring curls standing over bench with elastic band	**Progression:** Increase resistance by changing elastic band colour – red through to black
**Seated knee flexion**	Non weight-bearing	HG6. Seated knee flexion with elastic band	**Progression:** Increase resistance by changing elastic band colour – red through to black
**Standing hip extension**	Non weight-bearing	HG7. Hip extension with knee bent (90°) standing over a bench	
	Non weight-bearing	HG8. Hip extension with knee straight standing over a bench	
	Non weight-bearing	HG9. Hip extension with knee straight with elastic band standing over a bench	**Progression:** Increase resistance by changing elastic band colour – red through to black
**4. Calf strengthening**			
**Standing plantar-flexion**	Weight-bearing	C1. Double leg calf raises	
	Weight-bearing	C2. Single leg calf raises	
	Weight-bearing	C3. Double leg calf raises over edge of step	
	Weight-bearing	C4. Single leg calf raises over edge of step	
**5. Balance (if appropriate)**			
**Tandem stance**	Weight- bearing	B1. Maintain balance in tandem stance	**Progression:** remove hand support (if required), slowly raise arms in the air, eyes closed
**Natural stance**	Weight- bearing	B2. Maintain balance whilst tapping opposite foot forwards & backwards	
**Single leg stance**	Weight- bearing	B3. Maintain balance in single leg stance	**Progression:** Increase hold time up, slowly raise arms up and down, eyes closed

Physiotherapists also work with the patient to devise an individualised physical activity plan, with the aim of increasing physical activity to, or maintaining it at, recommended levels [30]. Participants use a wearable activity tracker to assist this and the physiotherapist and participant devise individualised step goals that are reviewed and modified (if required) at each consultation. Participants are encouraged to use the “Knee Plan and Log Book” for recording both their strengthening exercise program and physical activity plan after each consultation, and monitoring progress for discussion with the physiotherapist at the next consultation. Education about OA and its management occurs at all sessions, including discussion about the role of exercise and physical activity, including barriers to adherence and strategies for overcoming obstacles. Table 1 outlines the different education topics at each consultation.

Participants are encouraged and advised how to independently progress their exercise program and their physical activity plan between consultations, and beyond, once the physiotherapist consultations have ceased. Participants are encouraged to continue with their strengthening exercises and physical activity plan after the physiotherapist consultations have finished, up until the final outcome measurements are collected at 9 months. Participant use of monitoring and tracking tools (“Knee Plan and Log Book”; wearable activity tracker) is encouraged during the consultations, and beyond, to facilitate ongoing adherence to strengthening exercise and physical activity.

#### Mode of physiotherapy delivery

Face-to-face consultations – participants allocated to this group attend all of their consultations with the physiotherapist in the physiotherapist’s clinical practice rooms. Participants travel to and from the clinic at their own expense. Physiotherapists use their usual clinical methods for teaching the strengthening exercise program (ie demonstration, watching and correcting participant technique). Consultations are audio-recorded using digital audio recorders and uploaded by the physiotherapist to a secure password-protected cloud-based system.

Video consultations - participants allocated to this group attend all of their consultations using the video-conferencing facility of Zoom (Zoom Video Communications, Inc., USA), a commercial cloud-based system accessible from any internet-connected computer, laptop or mobile device. Physiotherapists consult from their clinic using a lap-top or desk-top computer, whilst participants are based at their home (or elsewhere if preferred). Instructions for accessing and downloading Zoom are provided to participants and participants are encouraged to independently set themselves up in readiness for their first consultation. Physiotherapists are given access to a bespoke website containing a video library of all exercises contained within the “Exercise Booklet” so that they can provide real-time demonstration of exercises to participants during video-conferencing, using the share-screen feature of Zoom. Participants do not have access to the online video library outside of the consultations. Video-conferencing consultations are video-recorded via Zoom and files are stored on a secure password-protected cloud-based system.

#### Treatment fidelity

Bespoke semi-structured consultation notes (paper-based or electronic according to physiotherapist preference) will be recorded by the physiotherapist for each consultation and returned to research staff at the completion of the participant’s series of consultations. Notes will be scrutinised by research staff for physiotherapist adherence to trial protocols. Fidelity will be recorded as the number and proportion of i) strengthening exercise programs prescribed by the second consultation; ii) physical activity plans prescribed by the second consultation; iii) follow-up consultations that reviewed strengthening programs; iv) follow-up consultations that reviewed physical activity plans; v) consultations where the RPE for the strength program was between 5 and 7; vi) all consultations that included education. The mean (SD) RPE for each participant’s strengthening exercise program will be determined over their consultations, as recorded in the treatment notes.

### Outcome measures

Table 4 summarises the schedule of enrolment, interventions and outcome measures for this RCT according to SPIRIT recommendations [16].

**Table 4 Tab4:**
[figure not shown]
Schedule of enrolment, interventions and assessments

#### Primary outcomes

There is no single common symptom that drives all people with knee OA to seek care from a physiotherapist. However, the two predominant reasons are for relief of knee pain and/or assistance with physical dysfunction [31, 32]. Furthermore, assessing both of these symptoms as quality indicators for the primary care of OA, is advocated [33, 34]. Thus we have chosen co-primary outcomes of change in i) pain; and ii) physical function, both of which are also specifically advocated for use in clinical trials in people with knee OA [35, 36]. The primary end-point is 3 months and the secondary end-point is 9 months. Change scores at each end-point are calculated using data measured at baseline, 3 months and 9 months using the following tools:

#### Severity of knee pain during walking

Average pain on walking in the last week is measured using an 11-point NRS with terminal descriptors ‘no pain’ (score = 0) and ‘worst pain possible’ (score = 10) from baseline, 3, and 9 months. This scale has demonstrated reliability in OA [37].

#### Physical function subscale of the Western Ontario and McMaster universities osteoarthritis index (WOMAC)

The Western Ontario and McMaster Universities (WOMAC) Osteoarthritis Index (Likert version 3.1) is used to assess limitations with physical functioning [38]. The self-reported tool is a disease-specific instrument which has established validity, reliability and responsiveness in an extensive range of OA studies [39]. The subscale contains 17 questions on knee function over the past week, with Likert response options from ‘no dysfunction’ (score = 0) to ‘extreme dysfunction’ (score = 4). Total score ranges from 0 to 68, with higher scores indicating worse function.

#### Secondary outcomes

For quality of life, physical activity and self-efficacy, change scores are calculated using data measured at baseline, 3 months and 9 months. Other secondary outcomes are measured at time-points as indicated below:

#### Health-related quality of life

Health-related quality of life is evaluated using the Assessment of Quality of Life (AQoL) (version AQoL-6D) [40]. The AQoL-6D contains 20 items that assess independent living, mental health, relationships, pain, coping and senses. Total scores range from − 0.04 to 1.00, with higher scores indicating better quality of life.

#### Physical activity levels

Physical activity over the previous week is assessed using self-report tool, the Physical Activity Scale for the Elderly (PASE) [41]. Total PASE scores range from 0 to over 400, with higher scores indicating greater physical activity.

#### Self-efficacy

Using the 8-item Arthritis Self Efficacy Scale [42], participants rate how certain they are that they can do 8 tasks using response options ranging from 1 (very uncertain) to 10 (very certain). Total scores are an average of the 8 items with a range from 1 to 10; higher scores indicate higher self-efficacy.

#### Participant-perceived global change

Participants rate their overall global i) change in pain, ii) change in physical function, and iii) change in physical activity at 3- and 9-months using separate 7-point Likert scales with terminal descriptors of ‘much worse’ to ‘much better’ [43]. For each scale, participants that indicate they are ‘moderately better’ or ‘much better’ are classified as ‘improved’ and all others as ‘not improved’.

#### Satisfaction with the physiotherapy consultations

Participants rate their satisfaction with the physiotherapy consultations at 3- and 9-months using a 7-point Likert scale with terminal descriptors of ‘extremely unsatisfied’ to ‘extremely satisfied’. Participants who report being ‘moderately satisfied’ or ‘extremely satisfied’ are classified as ‘satisfied’ and all others as ‘not satisfied’.

#### Therapeutic alliance

The Working Alliance Inventory Short Form [44] is scored separately by both the participant (at 3-months) and the physiotherapist (after the 5th consultation or on the day the 5th consultation was due to be scheduled for participants who cancel/do not attend). Overall scores range from 12 to 84, with higher scores indicating a stronger therapeutic alliance.

#### Convenience

Participants rate the convenience of their physiotherapy consultations at 3 months using an 11-point NRS with terminal descriptors of ‘extremely inconvenient’ (score = 0) and ‘extremely convenient’ (score = 10).

#### Attendance at consultations

Attendance at each consultation is recorded by physiotherapists in treatment notes, and by participants in an “Appointment Log Book”. The number of consultations attended, number of consultations cancelled/rescheduled, and number of consultations that were a “failed to attend” are reported throughout the 3-month intervention period.

#### Adherence with strengthening exercise program

At the 3-month and 9-month follow-up assessments, participants rate their adherence with their prescribed strengthening exercise program (“I have been doing my exercises exactly as I was asked to by my PEAK trial physiotherapist (number of sessions, exercises and repetitions)”) using an 11-point NRS (with terminal descriptors of ‘strongly disagree’ (score = 0) and ‘strongly agree’ (score = 10)). At each time-point, participants also self-report the number of strengthening exercise sessions performed over the previous week.

#### Adherence with physical activity plan

At the 3-month and 9-month follow-up assessments, participants rate their adherence with their physical activity plan (“I followed the physical activity plan that my PEAK trial physiotherapist helped me to develop”) using an 11-point NRS (with terminal descriptors of ‘strongly disagree’ (score = 0) and ‘strongly agree’ (score = 10)).

#### Co-interventions

Participants self-report any co-intervention use (medications for knee pain and any other treatments for knee OA) at baseline, 3, 6 and 9-months as part of the custom-developed survey collecting health service usage data (see below).

#### Adverse events

Participants who experience any adverse outcomes are instructed to discuss these with their physiotherapist, who institutes appropriate advice and/or changes to the strengthening exercise program and/or physical activity plan. Any risks to participants are likely to be minor and transient. In this trial, adverse events are defined as any problem experienced in the study knee or elsewhere in the body deemed by the participant to be a result of the exercises, physical activity plans and/or advice given by the physiotherapist AND at least one of i) that caused increased pain and/or interfered with function for 2 days or more, and/or ii) resulted in the participant seeking treatment from a health professional. Adverse events are ascertained by survey questions to participants at 3 and 9 months. The number and type of events are reported.

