Knee OA is mostly managed in primary care settings, with physiotherapists frequently involved in provision of care. Physiotherapy is traditionally provided during face-to-face consultations in the clinic. However, for many people, access to physiotherapy is hampered by geographical isolation and/or limited physiotherapy services. This is particularly a problem in regional and remote areas where services are often limited or non-existent. Face-to-face consultations also pose an infection risk for both the physiotherapist and the patient. This has been highlighted by the COVID-19 pandemic where many physiotherapy practices across the globe have restricted or ceased face-to-face consultations and instead shifted towards telehealth, in order to safeguard the health of both patients and staff.

We conducted the first RCT evaluating efficacy of video consultations with a physiotherapist for exercise management of knee OA [11]. We recruited 148 older people around Australia and compared video consultations (delivered by 8 different physiotherapists) combined with a self-directed online pain coping skills program, versus online education. Findings showed that the intervention significantly improved knee pain and physical function by clinically meaningful amounts at 3 months, and that benefits were sustained at 9 months. Furthermore, nested qualitative research showed that video consultations were acceptable to both patients and physiotherapists [12]. Patient convenience, flexibility, empowerment to self-manage and positive therapeutic relationships were emphasised by both patients and physiotherapists. Patients were very satisfied with the care they received and believed it was effective for them personally. These findings reflect survey data in people with knee OA [13] and in patients attending hospital-based physiotherapy screening clinics [14], as well as RCT findings in patients following joint replacement [15]. Collectively, research indicates most patients are willing to engage in video consultations for chronic musculoskeletal conditions. However, there is no research comparing the effectiveness of video-conferencing with physiotherapists to face-to-face consultations for people with knee OA.

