#### Cost-effectiveness outcomes

##### Health service usage

Participants retrospectively recall their health service usage for their knee pain and/or as a result of trial participation over 3-month intervals. Participants complete a custom survey to indicate the frequency of visits to health care providers for their knee pain, use of prescription and over the counter medication, injections, hospitalisation and investigative procedures at baseline, 3, 6 and 9 months.

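### The adverse-event definition leaves out harms of the delivery mode in both arms, so the safety summary is not a full comparison of video with face-to-face care

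*Protocol article*

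**What the plan says.** The Adverse events section of the protocol article sets a definition with two parts, both required.

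- **Cause.** The problem must be "deemed by the participant to be a result of the exercises, physical activity plans and/or advice given by the physiotherapist".
- **Severity.** It must have raised pain or impaired function for at least two days, or have "resulted in the participant seeking treatment from a health professional".

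The site is broad: "any problem experienced in the study knee or elsewhere in the body". On collection the section says "Adverse events are ascertained by survey questions to participants at 3 and 9 months", and on reporting, "The number and type of events are reported".

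Three other places bear on the point.

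- **Background:** "Face-to-face consultations also pose an infection risk for both the physiotherapist and the patient".
- **Mode of physiotherapy delivery**, on the face-to-face arm: "Participants travel to and from the clinic at their own expense". Video participants are at home or another place they prefer.
- **Health service usage**, under the cost-effectiveness outcomes: use of services is recalled "for their knee pain and/or as a result of trial participation".

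The Abstract lists safety, with effectiveness and cost-effectiveness, among the matters on which evidence for video consultations is lacking.

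**The concern.** The trial randomises the way a consultation is delivered. The Consultations section and Tables 1 to 3 give both arms the same five sessions, exercise protocol and behaviour-change components. The causal clause lists only that shared content. It does not mention attending, travelling to or taking part in a consultation, which is where the arms differ by design.

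What is at stake is how the safety result is read. A table of adverse events by arm in a trial of video against face-to-face care will be taken as a comparison of the safety of the two modes. Under this definition it compares only harms that participants put down to exercises, plans or advice. A real difference in mode-related harm could exist and not appear.

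**Working it through.** No stated figure is in dispute and the document gives no adverse-event rate, so the check is to apply the definition to the kinds of event that could arise.

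**Step 1: which part of the definition excludes.** The wide wording on site extends where a problem may occur, not what may have caused it. The treatment-seeking condition could be met by an infection or an injury. The causal clause is therefore the part that shuts mode-related harms out.

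**Step 2: apply it to examples.**

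| Example | Arm | Severity could be met? | Causal clause met? | Counted? |
|---|---|---|---|---|
| Knee flare put down to a prescribed exercise | either | yes | yes | yes |
| Injury put down to an exercise poorly taught or supervised through one mode | either | yes | yes | yes |
| Infection caught at the clinic | face-to-face | yes | no | no |
| Injury on the way to or from the clinic | face-to-face | yes | no | no |
| Problem from taking part by video, not put down to exercise or advice | video | yes | no | no |

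The second row shows that the definition is not blind to mode: if delivery changes how safely the exercises are done, those harms are counted. The last three rows show what it cannot register, and they fall in both arms.

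**Step 3: look for another route.** Table 1 has the physiotherapist ask about adverse events at consultations 2 to 5, and participants are told to discuss adverse outcomes with the physiotherapist. The stated means of ascertainment is nevertheless the participant survey at 3 and 9 months, under the definition above. The health service usage survey may pick up care that followed a mode-related harm, including hospitalisation, because its scope extends to trial participation. It would enter there as a cost item, not as an adverse event. No section of the article counts such a harm as an adverse event.

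**Step 4: what depends on it.** The aims at the end of the Background contain no safety objective. The Statistical analysis plan section states no safety hypothesis or margin. Non-inferiority rests on pain and function at 3 months, and the adverse-event definition does not enter it.

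**The case against.** The strongest reply is that safety has a modest, descriptive role here. The Abstract mentions it as a gap in the evidence, but the trial sets no aim or margin for it and promises only number and type of events. Related-event definitions are common, and this article condenses a fuller protocol in which serious-event reporting may be handled separately. All of this stands and limits the weight of the point. It does not remove it, because the article states the definition outright and that definition omits the feature that was randomised.

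Three stronger readings are tempting, and the document supports none of them.

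- **That the definition tilts the comparison against video.** A reader might infer this because travel and clinic attendance belong to the face-to-face arm, while harm from weaker correction of technique over video would be counted. But the clause is the same in both arms, video-related problems not put down to exercise or advice are dropped too, and no rates are given. The article nowhere names weaker correction as a known harm of video. It describes real-time demonstration by shared screen, and Table 1 has the physiotherapist watch new exercises in both arms.
- **That the number of lost events can be estimated.** One could take 197 participants × 5 consultations = 985 planned clinic visits and multiply by a rate. The document supplies no rate. Full attendance is not assured either: the sample size allows 15% loss to follow-up, and the per-protocol set requires only three consultations.
- **That the health service usage section contradicts the adverse-event section.** Its scope is wider because it serves costing. Two collections with different purposes may differ in scope without conflict.

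**Conclusion.** The point holds as a gap in coverage. Harms of the delivery mode (travel, clinic attendance including the infection risk that the Background names, and taking part by video) are not counted as adverse events in either arm. The adverse-event summary is therefore not a full safety comparison of the two modes and may miss a difference, including a possible advantage of video.

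The size and direction of what is missed cannot be derived from the document. The conclusion rests on reading the causal clause as written and on the article's definition being the one applied in the survey, whose wording is not shown. It is worth correcting because the correction is cheap, not because a primary conclusion is at risk.

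**What to change.** Extend the attribution clause so that it also covers problems the participant deems a result of attending, travelling to or taking part in the consultations. Keep the two severity conditions unchanged. Tag each event as exercise- or advice-related or as consultation-related, and report both categories by arm. Keep events under the current definition as a reportable subset, so that a count on the same basis exists for everyone.

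The cost is a wider survey item and one coding field. The downsides should be stated in the report. Recruitment began in November 2019, so participants already surveyed answered under the narrower definition, and the wider category can be reported only for those surveyed after the change. The Timelines section anticipates recruitment to August 2021 and completion by May 2022, so later surveys could carry it. Participants will often be unsure where an infection was caught, so attribution will be imprecise.

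Where the wider data are not available, label the count as exercise- and advice-related events only, and do not present it as the comparative safety of the two modes.
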